### Who will take informed consent? {26a}

Trained research assistants will take written informed consent. The informed consent process will occur in the language most comfortable for participants (usually in Setswana). Permission/assent will be documented by having the participant sign the permission/assent form or make a mark if the participant is illiterate; the latter will be witnessed by a third party. A copy of the informed consent/assent form will be offered to the participant. Staff will ensure that the participant takes a copy of a study contact card that contains study information and telephone numbers if the participant does not wish to take a copy of the permission/assent form.

### Additional consent provisions for collection and use of participant data and biological specimens {26b}

Not applicable, all our consent provisions are stated in the relevant section and we will not be collecting biological specimens.

## Interventions

### Explanation for the choice of comparators {6b}

(i)*Active comparator/treatment arm*: Our treatment arm will be composed of clinics with interventions for integrating hypertension and cardiovascular diseases care (InterCARE), namely, provider training on HTN/CVD, the use of adapted electronic health record (EHR)—especially electronic reminders, and use of treatment partners for PLWHIV with hypertension.(ii)*Placebo comparator/control arm*: Given our set of interventions as the treatment arm, the control arm will be composed of clinics without integrated care of HIV and hypertension. Care in these clinics is as usual, with no EHR modifications and no organized-updated training of health care workers on hypertension management. Thus, their training would have been at nursing/medical school or at some point in the past. Enrolled participants also do not have designated treatment partners. With this placebo comparator, hypertension is managed by a provider using any guidelines of their choosing.

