### Intervention description {11a}

The InterCARE package consists of three strategies adapted from the successful Botswana HIV program: provider training, use of an EHR, and treatment partners.*Electronic health records (EHR)*: at the beginning of the national ART program, Botswana developed a local EHR, patient information management system (PIMS) that has been used to document outcomes of the national ART program [9], and optimized for an HIV prevention trial [3]. However, this EHR system has not been used for other chronic diseases in Botswana. The use of clinical decision support in EHR is generally associated with improvement in quality of care [10], but data are mixed for CVD risk factors monitoring. This strategy can address barriers in knowledge and adoption of CVD risk assessment and HTN management and monitoring of national strategy key NCD care indicators.*Treatment partners*: many national HIV programs including in Botswana have utilized community members as treatment partners for PLWH [11–15]. In Botswana, the use of treatment partners has been associated with improved HIV medication adherence and viral suppression [11]. As with other chronic lifestyle-related medical conditions, family or presence of close other persons is recommended as part of an evidence-based strategy to assist those with hypertension to care for themselves, provide social support, promote adherence to lifestyle changes/medications, etc. [11]. This American Heart Association (AHA) evidence-based strategy for social support has not been adapted for PLWH with HTN in Botswana [16]. InterCARE participants will be given guidance on how to choose an appropriate treatment partner for their HTN support. Treatment partners will attend training along with the participant on how to provide social, emotional, and adherence support.*HTN/CVD training*: the highly successful KITSO training program (healthcare curriculum for HIV care in Botswana) is in use at more than 400 peri-urban and rural HIV clinics in Botswana but has never been leveraged to enhance NCD care for PLWH in Botswana. Building on the model, a dedicated healthcare provider curriculum and certification on hypertension control and CVD care among PLWH was developed for use in InterCARE, reflecting national and international guidelines for HTN management. The training will be provided at the start of InterCARE and again annually. Application and ongoing learning will be supported through practice facilitation by research nurses during regularly scheduled visits and monthly data audit and feedback.

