### Criteria for discontinuing or modifying allocated interventions {11b}

Criteria for discontinuing participant follow-up include withdrawal of consent, serious harm resulting from the trial, contamination/cross-over from one arm of the study to the other, and transfer from study sites to non-study sites. Criteria for modifying allocated interventions include significant changes in study site processes, for instance a change in EHR from PIMS (system in place at current trial sites) to IPMS (system available at other health centers in Botswana, but not yet part of the InterCARE sites) by intervention sites or from IPMS to PIMS by control sites.

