### Strategies to improve adherence to interventions {11c}

We believe that our EHR modifications to include prompts for recording anthropometry, cardiovascular disease risk factors, and blood pressure, among others, facilitate adherence to our intervention protocols. Furthermore, we have planned 6-monthly refresher trainings and retraining in sites where the staff turnover exceeds 50%. Pairing of patients with treatment partners will facilitate communication between them to support medication and lifestyle adherence as well as attendance of clinic appointments. We will also have patient/treatment partner booster sessions conducted via telephone: for patients with controlled BP, booster calls will take place about 3 months after initial clinic training session; for patients with uncontrolled BP, booster calls will take place on a monthly basis after initial clinic training, until BP is controlled.

Our DCF includes a question on self-reported medication adherence, we however do not directly monitor drug levels for adherence.

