### Outcomes {12}

The primary and secondary outcomes are based on the RE-AIM framework with effectiveness and implementation being the co-primary outcomes.

Primary and secondary effectiveness and implementation outcomes are fully described in Table 1. Exploratory secondary outcomes will include the extent to which participants are screened for other cardiovascular risk factors, counseled, and educated and documented in the EHR.

**Table 1 Tab1:** Effectiveness and implementation outcomes for InterCARE

Co-primary outcomes		
Effectiveness	Proportion of PLWH with diagnosed hypertension receiving anti-hypertensive medication with controlled blood pressure	EHR
Implementation	Proportion of clinic encounters in EHR where anti-hypertensive medications are prescribed if indicated	EHR
Secondary outcomes		Sources
Reach	· Proportion of eligible PLWH who agreed to be enrolled into InterCARE among those who met inclusion criteria · Proportion of PLWH who are aware of their hypertension status	· Modified EHR, DCF
Effectiveness	· Absolute difference in systolic and diastolic blood pressure between baseline, 12-month, and 24-month visits · The proportion of participants who scored > 70% on the heart disease fact questionnaire (HDFQ) · Proportion of PLWHIV with hypertension prescribed anti-hypertensive medications	· Modified EHR, DCF
Adoption	· Proportion of PLWH and HTN with 10-year CVD risk documented in EHR (E-CVDRF eval) · Proportion with BP documented in EHR · Proportion of those screened for other CVD risk factors using EHR · Proportion of those who received CVD risk factor counseling on anti-HTN medication, healthy diet, and appropriate physical activity levels · Proportion of PLWHIV with HTN enrolled in InterCARE receiving HTN and HIV care in the same clinic visit · Proportion of PLWHIV with HTN with BP control not on medication	· Modified EHR, DCF
Fidelity	· Proportion prescribed guideline concordant BP medication (as per Botswana 2016 Primary Care Guideline [17]) and/or major publication on management of BP among black Africans [18] · Proportion of treatment partners trained per protocol · Proportion of treatment partners providing support with the same frequency as expected · Proportion of intervention clinics that implemented the three components of InterCARE	· EHR, DCF, electronic trial logs
Feasibility	· Implementation of integrated HIV/hypertension care	· EHR, facility visit tracker, monitoring reports

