## Data collection and management

### Plans for assessment and collection of outcomes {18a}

#### PLWH and HTN

Following informed consent, study data from participating PLWH will be collected at baseline and then at study visits at months 6, 12, 18, and 24 for the PLWH and their treatment partners. Socio-demographics, co-morbidities, medication intake, cardiovascular health data including a blood pressure assessment, and treatment partner sessions will be collected in the study electronic database.

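### Both co-primary outcomes are sourced only from the EHR, and one intervention component changes that EHR in one arm, so ascertainment of the primary outcomes can differ by arm

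*Protocol article*

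**What the plan says.** **Outcomes {12}, Table 1.** The effectiveness co-primary is "Proportion of PLWH with diagnosed hypertension receiving anti-hypertensive medication with controlled blood pressure". The implementation co-primary is "Proportion of clinic encounters in EHR where anti-hypertensive medications are prescribed if indicated". The source column gives EHR alone for both. Most secondary rows add the data collection form (DCF).

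**Explanation for the choice of comparators {6b}.** The intervention includes "the use of adapted electronic health record (EHR)—especially electronic reminders", alongside provider training and treatment partners. For the control clinics: "Care in these clinics is as usual, with no EHR modifications".

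**Strategies to improve adherence {11c}.** The article describes "our EHR modifications to include prompts for recording anthropometry, cardiovascular disease risk factors, and blood pressure". The Intervention description {11a} adds monthly data audit and feedback, and says that "this EHR system has not been used for other chronic diseases in Botswana". Study setting {9} notes that clinics keep both paper and electronic records.

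**Plans for assessment and collection of outcomes {18a}.** At baseline and months 6, 12, 18 and 24, the study database receives "medication intake, cardiovascular health data including a blood pressure assessment". Neither co-primary is tied to these data.

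**Criteria for discontinuing or modifying {11b}.** PIMS is called the system in place at the trial sites, and IPMS is described as "not yet part of the InterCARE sites) by intervention sites or from IPMS to PIMS by control sites".

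**Missing data {20c} and blinding {17a}.** Missing outcomes are not imputed, and nobody is blinded.

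**The concern.** A between-arm comparison needs the outcome to be seen equally well in both arms. Here one arm's recording instrument is altered, prompted and audited, and the other's is left alone. The article itself treats recording as something the intervention changes: the share of patients with blood pressure documented in the EHR is an adoption outcome.

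A control patient who is treated and controlled, but whose care sits on paper, either counts as a failure or drops out. Either way, what is seen depends on the arm. The exposure is most direct for the implementation co-primary, where both the indication and the prescription must be in the EHR. At stake is whether a risk ratio on either co-primary reflects better hypertension care, better recording, or a mixture. A larger sample would not help, because this is bias and not imprecision.

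**Working it through.** **Inputs from the article.** 7 pairs of clinics, about 333 participants per clinic, within-clinic correlation 0.055, two-sided 5% level. Table 2 gives 57% vs 80% for prescribing (power 93%, detectable difference 22 points) and 19% vs 64% for effectiveness (power > 99%, detectable difference 21 points).

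**Assumed input.** The share of true events captured in the EHR is not in the article. The range used is 50% to 90% in control clinics, against 95% or 100% in intervention clinics.

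**Step 1: reproduce the plan's power.** The normal approximation for a pair-matched design with two pairs deducted is SE² = [1 + (m − 1) × ICC] × [p1(1 − p1) + p2(1 − p2)] / [m × (7 − 2)].
- Design effect: 1 + 332 × 0.055 = 19.26.
- Prescribing: SE² = 19.26 × (0.2451 + 0.1600) / 1665 = 0.00469, so SE = 0.0685. Then 0.23/0.0685 − 1.96 = 1.40, a power of 91.9% (stated 93%). The detectable difference is 22.3 points (stated 22).
- Effectiveness: power is above 99.9% (stated > 99%) and the detectable difference is 21.9 points (stated 21).

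The planned power figures hold to within 2 points, so the question is validity, not sample size.

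**Step 2: identical care, unrecorded counted as not prescribed.** Spurious difference = true rate × (intervention capture − control capture). With a true rate of 57% in both arms and intervention capture of 95%:

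| Control capture | Calculation | Spurious difference |
|---|---|---|
| 50% | 57 × 0.45 | 25.7 points |
| 70% | 57 × 0.25 | 14.3 points |
| 80% | 57 × 0.15 | 8.6 points |
| 90% | 57 × 0.05 | 2.9 points |

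Table 2 does not say whether its 57% is true or recorded prescribing. If it is already recorded, the calculation runs the other way: with true prescribing of 80% in both arms and full capture in intervention clinics, control capture of 57/80 = 71% shows 57% vs 80%.

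**Step 3: effectiveness, unrecorded counted as not controlled.** With true control of 40% in both arms and full capture in intervention clinics, control capture of 19/40 = 47.5% shows 19% vs 40%, the 21-point detectable difference. To show the planned 19% vs 64% with no difference in care, control capture would have to be 19/64 = 30%.

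**Step 4: unrecorded cases leave the denominator.** Take a true rate of 57% in both arms and 95% capture of everything in intervention clinics, which show 57%.
- Control clinics capture 50% of both treated and untreated cases: they also show 57%, so there is no bias.
- Control clinics capture 90% of treated and 50% of untreated cases: 0.513/(0.513 + 0.215) = 70.5%, a spurious difference of 13.5 points against the intervention.
- Control clinics capture 50% of treated and 90% of untreated cases: 0.285/(0.285 + 0.387) = 42.4%, a spurious difference of 14.6 points in its favour.

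The sign depends on which cases go unrecorded and how they are classified.

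**The case against.** The defence has several good arguments.

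- **Cross-checks exist.** In Table 1, change in systolic and diastolic pressure and the proportion prescribed medication draw on the modified EHR and the DCF; maintenance of control draws on the EHR and the DCF. Documentation of blood pressure is a separate outcome. A reader might infer that the trial cannot tell care from recording at all. That goes too far, because these secondary outcomes give a partial check. They do not change what the co-primaries rest on.
- **The EHR is one of three components.** Training and treatment partners may improve care in their own right, so a reader should not infer that recording alone explains a positive result.
- **Capture rates are assumptions.** This stands. The 22-point figure in Table 2 also belongs to an adoption row that starts from 57%, so it is only a rough yardstick for the co-primary.
- **The 0% and 2% recording rates in Table 2** concern waist and hip circumference and calculated 10-year CVD risk. They do not show that prescriptions or blood pressure go unrecorded in control clinics.
- **The implementation co-primary is an encounter-level measure.** Moving it to a six-monthly form that records medication intake would make it a different outcome. This stands, and the fix respects it.
- **The article may condense a fuller protocol.** But Table 1 is not silent: it names a source for the co-primaries and omits the DCF that it lists for other outcomes.

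**Conclusion.** The concern holds as a risk of arm-dependent ascertainment of both co-primaries, built in by the Table 1 source column. Its size cannot be fixed from the article. Under the assumed capture rates and a true prescribing rate of 57%, it runs from about 3 to about 26 points when unrecorded means not prescribed, and it can take either sign when unrecorded cases are excluded. For effectiveness, recording alone is unlikely to yield the planned 45 points. It could reach the 21-point detectable difference only with control capture near or below one half, at a true control rate of 40%.

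A reader might also infer from {11b} that the arms run on different EHR systems. The article does not establish that: the clause on control sites leaving IPMS conflicts with the statement that IPMS is not yet at the trial sites. This is an inconsistency to resolve, and only weak evidence of a difference between arms.

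**What to change.** 1. **Effectiveness co-primary.** Change the Table 1 source to the study-visit blood pressure and medication data in {18a}, collected on the same schedule in both arms. Keep the EHR-derived version as a sensitivity analysis. State who measures the study-visit blood pressure, which {18a} leaves open, and how a participant with no recorded pressure or treatment is classified.
2. **Implementation co-primary.** Keep the encounter-level EHR definition, but interpret it as recorded prescribing. Support it with the person-level DCF medication data compared between arms, noting that medication intake is not the same as a prescription at each encounter.
3. **EHR systems.** Reconcile the two statements in {11b} so that the system used by control sites is clear.

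**Cost.** No new data are needed for item 1. It does need a formal amendment with the approvals listed under {25}, after recruitment closed on 11 September 2023 and with unblinded analysts, so the reason should be documented and both versions reported. The effectiveness result would then reflect study-visit rather than routine-care measurement.

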### Intervention description {11a}

The InterCARE package consists of three strategies adapted from the successful Botswana HIV program: provider training, use of an EHR, and treatment partners.*Electronic health records (EHR)*: at the beginning of the national ART program, Botswana developed a local EHR, patient information management system (PIMS) that has been used to document outcomes of the national ART program [9], and optimized for an HIV prevention trial [3]. However, this EHR system has not been used for other chronic diseases in Botswana. The use of clinical decision support in EHR is generally associated with improvement in quality of care [10], but data are mixed for CVD risk factors monitoring. This strategy can address barriers in knowledge and adoption of CVD risk assessment and HTN management and monitoring of national strategy key NCD care indicators.*Treatment partners*: many national HIV programs including in Botswana have utilized community members as treatment partners for PLWH [11–15]. In Botswana, the use of treatment partners has been associated with improved HIV medication adherence and viral suppression [11]. As with other chronic lifestyle-related medical conditions, family or presence of close other persons is recommended as part of an evidence-based strategy to assist those with hypertension to care for themselves, provide social support, promote adherence to lifestyle changes/medications, etc. [11]. This American Heart Association (AHA) evidence-based strategy for social support has not been adapted for PLWH with HTN in Botswana [16]. InterCARE participants will be given guidance on how to choose an appropriate treatment partner for their HTN support. Treatment partners will attend training along with the participant on how to provide social, emotional, and adherence support.*HTN/CVD training*: the highly successful KITSO training program (healthcare curriculum for HIV care in Botswana) is in use at more than 400 peri-urban and rural HIV clinics in Botswana but has never been leveraged to enhance NCD care for PLWH in Botswana. Building on the model, a dedicated healthcare provider curriculum and certification on hypertension control and CVD care among PLWH was developed for use in InterCARE, reflecting national and international guidelines for HTN management. The training will be provided at the start of InterCARE and again annually. Application and ongoing learning will be supported through practice facilitation by research nurses during regularly scheduled visits and monthly data audit and feedback.

These strategies from the HIV program were refined through key partner engagement including patient groups, healthcare professionals, Ministry of Health (MoH) representatives (Information Technology, HIV program, NCD program), implementation science experts, and biostatisticians. After adaptation, these implementation strategies were piloted over a 12-month period in two clinics to test feasibility, adoption, acceptability, and fidelity. After the pilot completion, the same partner groups were reconvened to provide input for further adaptation as needed for use in the InterCARE trial.

### Criteria for discontinuing or modifying allocated interventions {11b}

Criteria for discontinuing participant follow-up include withdrawal of consent, serious harm resulting from the trial, contamination/cross-over from one arm of the study to the other, and transfer from study sites to non-study sites. Criteria for modifying allocated interventions include significant changes in study site processes, for instance a change in EHR from PIMS (system in place at current trial sites) to IPMS (system available at other health centers in Botswana, but not yet part of the InterCARE sites) by intervention sites or from IPMS to PIMS by control sites.

### Strategies to improve adherence to interventions {11c}

We believe that our EHR modifications to include prompts for recording anthropometry, cardiovascular disease risk factors, and blood pressure, among others, facilitate adherence to our intervention protocols. Furthermore, we have planned 6-monthly refresher trainings and retraining in sites where the staff turnover exceeds 50%. Pairing of patients with treatment partners will facilitate communication between them to support medication and lifestyle adherence as well as attendance of clinic appointments. We will also have patient/treatment partner booster sessions conducted via telephone: for patients with controlled BP, booster calls will take place about 3 months after initial clinic training session; for patients with uncontrolled BP, booster calls will take place on a monthly basis after initial clinic training, until BP is controlled.

Our DCF includes a question on self-reported medication adherence, we however do not directly monitor drug levels for adherence.

### Relevant concomitant care permitted or prohibited during the trial {11d}

Patients in both the intervention and control arms will continue to receive concomitant care for all the comorbidities, and we do not prohibit them from receiving any interventions during the trial.

### Provisions for post-trial care {30}

Participants with uncontrolled blood will be referred to their primary health care workers for optimization of blood pressure. Adverse events will be reported as per protocol and Botswana Medicines Regulatory Authority (BOMRA). Given the nature of our implementation science trial, we do not anticipate frequent nor serious harm as a direct effect of our study. We do not offer any compensation to those who could suffer harm from being on treatment for hypertension treatment.

